### Monitoring

Regular monitoring will be conducted by HC & Management Inc. independently from the study sponsor to control data quality. They will confirm whether the record of the case report form is accurate by comparing it to the source and whether the practical procedures of the trial follow the approved protocol.

### Ethics

The IRBs of the Korean Medicine Hospital of Wonkwang Gwangju and of Sanbon University have approved the protocol (IRB approval numbers 2016-5-4 and 2016-34-01, respectively). This study is registered with the national clinical trial registry Clinical Research Information Service, which is a primary registry of the World Health Organization International Clinical Trials Registry Platform (KCT0001984). An Investigational New Drug status (30731) was granted by the Korea Food and Drug Administration. Any protocol modifications will be approved by the IRBs and the Korea Food and Drug Administration prior to implementation.

## Discussion

There are large variations in the reported annual incidence of ALS in Europe, Asia, and North America, ranging from 2.1 to 8.5 per 100,000 population [26]. There is currently no known method for a permanent cure for ALS using conventional medicine [27]. Thus, patients with ALS may attempt to visit a multidisciplinary clinic or use complementary and alternative medicine [28, 29].

Prior studies have shown that Mecasin, a herbal extract, has neuro-protective and anti-neuroinflammatory effects, and its safety has been proven in both in vitro and in vivo trials [8–14]; it has been shown to reduce the progression of ALS in Korean Medicine Clinics [6, 7]. No previous randomized controlled trial has examined the effects of Mecasin for the treatment of ALS. The planned clinical trial will determine the optimal dosages of Mecasin and will show whether combined Mecasin and riluzole treatment is both effective and safe for patients with ALS Additional file 1.

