**Methods:**

This is a phase II-A, multi-center, randomized study with three arms. Thirty-six patients with ALS will be randomly assigned to one of three groups, each receiving the standard treatment with 100 mg of riluzole in addition to one of 1.6 g of Mecasin, 2.4 g of Mecasin, or a placebo. The Primary outcome is the Korean version of the Amyotrophic Lateral Sclerosis Functional Rating Scale-Revised result after 12 weeks of treatment. Secondary outcomes include results of the Short Form Health Survey-8, Medical Research Council Scale, Visual Analogue Scale for Pain, Hamilton Rating Scale for Depression, Fatigue Severity Scale, Patient Global Impression of Change, pulmonary function test, forced expiratory volume in 1 s and its ratio to forced vital capacity, creatine kinase, and body weight. The frequencies of total adverse events and serious adverse events will be described and documented. The trial protocol has been approved by the Institutional Review Board of the Wonkwang University Gwangju and Sanbon Hospital (2016–5-4 and 2016–34-01, respectively). An Investigational New Drug status (30731) was granted by the Korea Food and Drug Administration.

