**Discussion:**

This trial will aim to identify the optimal dosage of Mecasin. Additionally, it will test the efficacy and safety of Mecasin in conjunction with standard treatment, riluzole, for alleviating the functional decline in patients with ALS.

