### Secondary objectives

The secondary objectives are to determine whether Mecasin, combined with standard ALS treatment, significantly slows the rate of functional deterioration in patients with ALS over 12 weeks, compared with standard treatment alone, and to monitor the safety of Mecasin combined with standard ALS treatment over 16 months. We also aimed to determine whether this treatment affects health-related quality of life, depression, muscle strength, pain, fatigue, pulmonary function, creatine kinase, or body weight in patients with ALS over 12 months.

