### Sample size

The primary purpose of this trial is to investigate the appropriate dosage for Mecasin, and to examine the efficacy and safety of Mecasin combined with the standard treatment, riluzole. Considering a dropout rate of 20%, 12 participants will be assigned to each of the three groups.

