### Adverse events

All undesirable medical findings that have not been observed prior to the clinical trial will be classified as adverse events. All unexpected responses related to Mecasin and riluzole will be recorded. If serious adverse events occur, these will be notified to the sponsor, Hanpoong Pharm and Foods Co., the Institutional Review Board (IRB), and the Ministry of Food and Drug Safety. The number of adverse events in the two Mecasin groups will be compared using the χ^2^ or Fisher’s exact tests.

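### The only stated safety test compares the two Mecasin doses with each other and omits placebo, so it cannot answer whether Mecasin plus riluzole is safe

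*Protocol article*

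**What the plan says.** The Discussion section of the protocol article says the trial "will show whether combined Mecasin and riluzole treatment is both effective and safe for patients with ALS". The Discussion paragraph of the abstract says "it will test the efficacy and safety of Mecasin in conjunction with standard treatment, riluzole". Under Secondary objectives the aim is "to monitor the safety of Mecasin combined with standard ALS treatment over 16 months", with no criterion attached.

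The Adverse events section gives one inferential rule: "The number of adverse events in the two Mecasin groups will be compared using the χ^2^ or Fisher’s exact tests". Placebo is not named in that comparison. The Methods paragraph of the abstract adds a descriptive element: "The frequencies of total adverse events and serious adverse events will be described and documented".

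On size, the Sample size section says: "Considering a dropout rate of 20%, 12 participants will be assigned to each of the three groups". The article gives no expected adverse-event rate, no significance level for the adverse-event test and no tolerable excess of harm.

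**The concern.** The question posed is whether Mecasin added to riluzole is safe. The comparison that bears on it is each Mecasin arm against riluzole plus placebo, which this randomized, blinded design supplies. The stated test instead contrasts 1.6 g with 2.4 g. It answers a dose question, and it says nothing about harm common to both doses.

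There is a second problem behind the first. Naming placebo in the same test would give the right contrast, but with 12 patients per arm a p-value would usually be non-significant even with a sizeable excess of affected patients.

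What is at stake is the dose choice, which is the primary objective. A null dose-versus-dose test, set beside a promise to show whether the combination is safe, could be carried forward as reassurance that the data do not contain.

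**Working it through.** **Inputs from the article.** Three arms of 12, allocated 1:1:1; a chi-square or Fisher's exact test between the two Mecasin groups.

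**Assumptions, because the article gives no figure.** Two-sided 5% level. The unit is the patient with at least one adverse event, since both tests need independent units and the text speaks only of the number of events. Comparator event rates are 10%, 20% and 30%. All 12 patients per arm are counted.

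**No figure of the plan to reproduce.** The article attaches no power or event rate to its 12 per arm, so there is no safety calculation to check.

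**Method.** For arms of size n1 and n2 with true rates p1 and p2, the miss rate is the sum, over all tables (a, b) with test p > 0.05, of Bin(a; n1, p1) × Bin(b; n2, p2). This is exact enumeration.

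**Step 1: the test as written (dose v dose, 12 v 12), same true rate in both doses.** The chance of a non-significant Fisher result is 98.3% at a shared rate of 30%, 97.9% at 40%, 97.7% at 50% and 97.9% at 60%. With uncorrected chi-square it is about 94–95% at these rates. The placebo rate does not enter the calculation, so the answer is the same whether placebo runs at 5% or at 50%. More patients would not change this.

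**Step 2: the same test with placebo as comparator, 12 v 12.** Percentage of trials in which the excess is missed:

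| Excess | Placebo v Mecasin | Fisher | Uncorrected chi-square |
|---|---|---|---|
| 20 points | 10% v 30% | 91% | 80% |
| 20 points | 20% v 40% | 91% | 82% |
| 30 points | 10% v 40% | 77% | 61% |
| 30 points | 20% v 50% | 79% | 64% |
| 30 points | 30% v 60% | 79% | 64% |
| 40 points | 10% v 50% | 58% | 40% |
| 40 points | 20% v 60% | 61% | 43% |
| 50 points | 10% v 60% | 36% | 21% |
| 50 points | 20% v 70% | 39% | 23% |

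Pooling both doses against placebo (24 v 12, Fisher) still misses 85% at 10% v 30%, 61% at 10% v 40% and 65% at 20% v 50%.

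**Step 3: what this means in counts.** Against 0/12, Fisher needs at least 5/12 for p < 0.05 (p = 0.037); 4/12 v 0/12 gives p = 0.093. With 6/12 v 2/12, Fisher p = 0.19, while the Newcombe 95% interval for the risk difference runs from −4 to +61 points. The interval shows what the p-value hides.

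**Step 4: what the data could exclude.** With no events in n patients, the one-sided 95% upper bound on the true rate is 1 − 0.05^(1/n).
- n = 12: 1 − 0.05^(1/12) = 22.1%.
- n = 24 (both Mecasin arms): 1 − 0.05^(1/24) = 11.7%.

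**The case against.** Safety in a phase II-A trial is normally descriptive, and 12 per arm is not in itself a fault. The abstract plans to describe adverse and serious adverse event frequencies. The schedule table includes blood tests, an electrocardiogram and adverse-event assessment up to the week 16 follow-up, and a clinical view can be formed from these. Interval methods may also sit in a full protocol or analysis plan that is not shown.

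All of this stands, and low power and unstated intervals are not the finding. What it does not answer is the mismatch on the page: a stated aim to learn whether the combination is safe, and a stated test that leaves out the only arm able to show it. The mention of described frequencies does not repair a comparison that has been fixed between the wrong arms.

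Stronger readings are tempting and should be resisted:
- A reader might infer that the article promises Mecasin will be shown to be safe. It says whether, not that.
- A reader might infer that a non-significant test will be declared evidence of safety. No section says so.
- A reader might infer that any large harm would usually be missed. The table in the working does not bear that out: at 50 points both tests detect the excess in most trials, and at 40 points uncorrected chi-square does too.

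**Conclusion.** The point holds in a limited form. As written, the adverse-event test cannot inform harm over riluzole plus placebo at any sample size, because an excess shared by both doses leaves it non-significant about 98% of the time (Fisher). Adding placebo to the same test would correct the contrast, but excesses of 20 to 30 points would still be missed in about 77–91% of trials by Fisher and 61–82% by uncorrected chi-square. A non-significant result could therefore not support a conclusion of safety, whether or not anyone intends to draw one.

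The miss rates rest on assumed event rates, an assumed two-sided 5% level and counting patients rather than events. The absence of placebo from the stated comparison rests on none of these. The change is worth making: it replaces an uninformative comparison with an informative one, using data the trial already collects.

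**What to change.** In the Adverse events section:
- For each of the three arms, report the proportion of patients with any adverse event and with any serious adverse event, with exact (Clopper-Pearson) 95% limits.
- For each Mecasin dose against riluzole plus placebo, report the risk difference with a 95% interval, for example Newcombe's.
- Keep the dose-versus-dose comparison as supplementary.
- State that a non-significant test will not be taken as evidence of safety.

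In the Discussion paragraph of the abstract and the Discussion section, restate the safety aim as a preliminary description of the adverse-event profile, together with the rate of harm that the data can exclude. If no events of a given kind occur, that is a one-sided 95% upper bound of about 22% for an arm of 12 and about 12% across the 24 Mecasin patients.

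The cost is wording and a few intervals from data already collected, with no added patients or procedures. The downside is a more modest safety claim.

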## Trial status

Recruitment for this trial opened in August 2016 and will close in February 2018. At the time of manuscript submission, the trial was in the recruitment phase.
